### Procedure

We Are Family will be responsible for contact with parents and organising study logistics (e.g., booking venues). The data collection and media screening sessions will be conducted face-to-face, in person with a team of moderators trained to deliver the research protocols (by KG and NC). There will be approximately 12 children with one of their respective parents per session. At T1, participants will arrive and be welcomed to the venue. The venue includes an initial waiting area and a main space where the child-interviews will take place. The main space will comprise of 12 booths around the edge, each with a table and two chairs, including a chair placed outside the booth for each parent to sit on. Once welcomed, participants will engage in five minutes of group play, facilitated by a moderator, to allow children to relax and become familiar with the environment. Next, participants will engage in a brief play activity with their allocated moderator to act as an ice breaker to the interview schedule. A moderator will complete the pre-interview (T1) with their assigned child (i.e., one moderator to one child) while their parent is encouraged to sit outside the booth. The pre-interview will commence with the child providing verbal assent (they will be told what to expect of the session and asked if they are happy to take part) and is expected to last up to 15 min.

As soon as the child has completed their interview, they will be given a tablet and two sets of headphones (one for the child and one for the parent) and asked to watch their assigned media together however they choose (e.g., sat on the floor, standing, on a chair). The moderator will remain close to the booth to provide any assistance if needed but will primarily be noting down any observations (e.g., engagement levels). Those in the music video conditions will be instructed to watch a 10-minute neutral video (i.e., Numberblocks) on a tablet, before they view their music video. This is to ensure each condition moves on to the post-interview at roughly the same time.

Immediately following the screening of their allocated media content, children will complete the post-interview (T2), with a moderator. While this is happening, parents will be asked to complete a paper-and-pen questionnaire. Once finished, participants will be thanked for their time and children will receive a small gift (e.g., stickers). Each parent will receive a secure link to their assigned media and will be encouraged to watch it again with their child at home over the next seven to ten days. Snacks and water will be available for children to have before, during, or after the session.

Approximately seven to ten days later, children will attend a follow-up session (T3) accompanied a parent. Children will engage in a follow-up interview with a moderator (i.e., the same format as T1 and T2). Following the completion of this third interview, parents will be provided with a debrief form which will include the explicit study aims, the condition they were allocated in, and details of mental health resources available for parents and children. Finally, to compensate participants for their time, We Are Family will organise thank you incentives. Parents will receive £130 in the form of cash payment, voucher, or donation to a charity of participant’s choice, and children will receive another small gift (e.g., stickers) and a certificate. See the schedule of enrolment, interventions and assessments in Fig. 4. The SPIRIT checklist is presented in Supplementary File 2.

**Fig. 4 Fig4:**
[figure not shown]
Schedule of recruitment, interventions, and outcome measures (SPIRIT)

### Statistical power and sample size

A proposed sample of 440 children aged 4–6 years and a corresponding parent will be recruited for this study. The study has been powered for immediate post intervention effects to be assessed using analysis of covariance with the commensurate baseline measure as the covariate. Caution has been exercised for assumed for effect size due to a universal non-clinical population undergoing a micro-intervention. This is offset by an assumed medium to large pre- post- correlation due to the short time interval between measures and the high degree of internal validity at data collection. For a two-sided test (alpha = 0.05), a sample size of *n* = 103 per arm will have 90% power for an assumed standardised effect of Cohen’s delta = 0.3, with pre-post-correlation of 0.75. A sample size of *n* = 92 per arm will have 80% power for a standardised effect of Cohen’s delta = 0.25 with pre- post- correlation of 0.8. The aim is to sample for *n* = 105 per arm (90% power, *r* = 0.75, *d* = 0.3). To achieve sample size, the target recruitment will be inflated to *n* = 110 per arm to compensate for any missing data.

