#### Pilot study

A small internal pilot study was conducted at the end of 2023 for the purpose of trialling the research design and protocols. A stop-go protocol was implemented, and progression criteria was based on; (1) feasibility assessment such as participant recruitment, retention, and evidence of ceiling/floor effects on the primary outcome measure and (2) harm assessment including evidence of child distress due to the content / research process reported by children, parents, or moderators. Criteria was rated for each parameter with a traffic light system of green, amber, and red as seen in Table 1.

**Table 1 Tab1:** Stop-go progression criteria

Criteria			Green	Amber	Red
1. ***Feasibility assessment***					
Participant recruitment	*How many participants showed up at T1?*		**More than 80%** Continue to main trial	**Between 60–80%** Consult research team and review recruitment plans	**Less than 60%** Pilot study may need to be extended
Participant retention at T3	*How many participants showed up at T3?*		**More than 80%** Continue to main trial	**Between 50–80%** Consult research team and discuss strategies to increase retention	**Less than 50%** The main trial will need to reconsider the inclusion of T3
Ceiling and/or floor effects on the primary outcome	*Is there evidence of ceiling or floor effects at T1 on the primary outcome measure*,* child body appreciation?*		**No** Continue to main trial	**Partial** Consult research team and discuss potential measure amendments	**Yes** The main trial will need to potentially reconsider the response scale for the primary outcome
2. ***Harm assessment***					
Child distress	*Were any of the children visibility distressed?*,* did any of the children tell the moderators anything concerning?*,* did any parent withdraw their child during the pilot due to the content or research process?*		**None** Continue to main trial	**Between 1–10%** Review feedback from moderators and parents, consult with the research team	**More than 10%** All cases to be qualitatively investigated and the team to consider the safety of the trial

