A total of 80 children were enrolled, of which 63 attended. On the day, one child refused to take part, and one child struggled to focus on the tasks making it hard for them to participate, resulting in usable data from 61 children and their accompanying parent. Insights from the pilot allowed us to modify the moderator guide to specify what needed to be said verbatim, versus what could be adapted to suit the individual needs of the child. Additionally, the option for children to choose which order to complete each game/measure was removed to streamline the procedure and reduce participant time burden. Further, we identified ways to reduce the influence of the moderator on children’s responses, by randomising the order of the weight bias images, instructing moderators to not pass comment during the weight bias activity (e.g., “thank you”, “great”), and throughout the moderation, avoiding the use of ticks, crosses, or red pen on their moderator forms.

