The above analysis plan for body appreciation will be repeated for the secondary outcome measures of functionality appreciation and weight bias. Secondary research questions at T3 will be examined using the same analysis of covariance methods controlling for baseline (T1).

The aim is to have ITT data on *N* = 420 participants. This will be achieved through a target recruitment of *N* = 440 cognisant that some potential participants might be unable to partake in the research due to external mitigating reasons. If the size of the ITT analysis set is N > = 380 then the data will be analysed as given. If the size of the ITT analysis set due to missing data is between 260 and 380 then a full missing values analysis will be undertaken, and appropriate sensitivity analyses performed. If the size of the ITT analysis set due to missing data is less than 260 then results will be given descriptively.

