Despite several strengths, there are some limitations, mainly related to the challenges of working with very young children. First, scant body image measures were available for administration among 4–6-year-olds. As such, the measures described in this paper were purpose built or were adapted from the few age-appropriate measures available. Although the measures were carefully developed with body image experts, informed by current evidence and several rounds of public involvement feedback, further research beyond the scope of this study will be required to conduct a rigorous validation to examine their psychometric properties. We believe this is an important next step in being able to advance the understanding of young children’s body image.

Similarly, the quality of the self-report data we obtain from this age group may vary. Due to children’s developmental capacity around ages 4 to 6 years, uncertainties persist regarding the amount of unusable data that may be collected (e.g., non-sensical responses, child refusal to engage or interact, or simply a lack of comprehension of the questions). From the beginning of the project, our measures and processes were thoroughly informed by public involvement work to mitigate the likelihood of unusable data. Nevertheless, an awareness that some participant responses may be unusable has been factored into our power calculations. It is hoped that by conducting this work and being transparent in our research endeavours, we can shed light on these issues for other researchers to learn from.

Designing and evaluating interventions through a collaborative process between academics, creatives partners and industry as described in this protocol paper is hugely beneficial for many reasons. All stakeholders bring different skills and expertise, together ensuring interventions are developed to be as acceptable and enjoyable to the target group as possible, while also grounded in a scientific evidence-base. Academic partners bring the scientific knowledge including current evidence on attitudes and behaviour change, as well as rigorous research methods. The creative partners bring the academic messaging to life through storytelling, animation, and humour. Finally, industry partners can maximise intervention reach. If proven to be effective, these stand-alone media micro-interventions have potential to reach hundreds of thousands of young children in many countries across the world.

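### The 4.5% allowance from 440 recruited to 420 analysed does not reflect the 24% loss in the trial's own pilot; at that rate power is about 83%, not 90%

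*Protocol article*

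**What the plan says.** Statistical power and sample size: 103 children "per arm will have 90% power for an assumed standardised effect of" d = 0.3 with a pre-post correlation of 0.75. A second scenario gives 80% power at 92 per arm for d = 0.25 and r = 0.8. The aim is 105 analysed per arm, and "the target recruitment will be inflated to *n* = 110 per arm to compensate for any missing data".

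Statistical analyses: the same margin appears as 440 recruited to give 420 in the ITT set, and it is meant to cover children who cannot take part. The ITT set needs some outcome data at T2 or T3. At 380 or more, the data are analysed as they stand. The next rule begins "If the size of the ITT analysis set due to missing data is between 260 and 380 then a full missing values analysis". Below 260, results are descriptive only.

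Recruitment: the research agency randomises after consent, and parents receive the session details only after allocation.

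Pilot study: "A total of 80 children were enrolled, of which 63 attended"; one child then refused and one could not focus, "resulting in usable data from 61 children and their accompanying parent". Table 1 rates attendance of 60% to 80% as amber, with the action "Consult research team and review recruitment plans".

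Discussion: "an awareness that some participant responses may be unusable has been factored into our power calculations".

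**The concern.** The article gives both an allowance for loss and an observed loss, and the second is about five times the first. The sample-size section does not mention the pilot result. Because allocation precedes attendance and the ITT set requires post-baseline data, a randomised child who never attends drops out of the analysis and uses up the margin.

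Two things are at stake. The 90% power is conditional on 105 analysed per arm, which the recruitment target may not deliver, so a null result could be read as coming from a better-powered trial than it was. And the missing-values rule, written as a contingency, would become the normal route to the main result.

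**Working it through.** **Inputs.** Two-sided alpha 0.05; d = 0.3 with r = 0.75 and d = 0.25 with r = 0.8; 103, 105 and 110 per arm (Statistical power and sample size). 440, 420, 380 and 260 in total (Statistical analyses). 80 enrolled, 63 attended, 61 usable (Pilot study). Each main comparison uses two equal arms.

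**1. The plan's own figures.** For ANCOVA, n per arm = 2(1 − r²)(z₀.₉₇₅ + z_power)² / d².
- d = 0.3, r = 0.75, 90%: 2 × 0.4375 × (1.960 + 1.282)² / 0.09 = 102.2, so 103. Stated: 103.
- d = 0.25, r = 0.8, 80%: 2 × 0.36 × (1.960 + 0.842)² / 0.0625 = 90.4, so 91. Stated: 92.

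Both are sound. Only the allowance for loss is in question.

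**2. Allowance.** (440 − 420)/440 = 5/110 = 4.5%. The threshold for analysing the data as they stand allows (440 − 380)/440 = 13.6%.

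**3. Pilot loss.**
- Attendance: 63/80 = 78.75%, which is amber in Table 1.
- Usable: 61/80 = 76.25%, so the loss is 19/80 = 23.75%. The exact 95% CI for the loss is 14.9% to 34.6%, which excludes both 4.5% and 13.6%.
- Of the 19 lost, 17 did not attend. Among attenders the loss was 2/63 = 3.2%.

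**4. Expected analysed number at the pilot rate.** 440 × 61/80 = 335.5, about 336; per arm 110 × 61/80 = 83.9, about 84. Over the CI the total is 288 to 374, all below 380.

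**5. Power at that number.** Power ≈ Φ(d / √(2(1 − r²)/n) − 1.960).
- d = 0.3, r = 0.75, n = 83.9: Φ(2.937 − 1.960) = 83.6%. The noncentral t gives 83.2%, and 77% to 87% over the CI.
- d = 0.25, r = 0.8, n = 83.9: Φ(2.698 − 1.960) = 77.0%, against the stated 80% at 92 per arm.

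**6. Other rates of loss** (d = 0.3, r = 0.75, normal approximation):

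| Loss | Analysed | Power |
|---|---|---|
| 5% | 418 | 90.6% |
| 10% | 396 | 89.1% |
| 15% | 374 | 87.3% |
| 20% | 352 | 85.3% |
| 23.75% | 335.5 | 83.6% |
| 30% | 308 | 80.4% |

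**7. Chance of reaching 380.** With the uncertainty of the pilot rate included (beta-binomial prediction, Jeffreys prior), it is about 1.4%; the chance of landing between 260 and 379 is about 98%.

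**8. If 440 counts attenders.** Only the 2/63 applies: 440 × 61/63 = 426 analysed, 106.5 per arm, with 91% power. The shortfall disappears.

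**The case against.** The strongest reply is that everything turns on when the 440 is counted. The section on moderator fidelity speaks of interviewing 440 children, which could mean children seen, and step 8 shows that the concern then fails. The rest of the article points the other way. Recruitment places randomisation before attendance, Statistical analyses says the 440-to-420 margin covers children unable to take part, and the fidelity section uses 80 for the pilot, which is the number enrolled and not the 63 seen. The condition must be stated, but the enrolment reading is the better supported.

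Attendance may also improve. At 78.75% it was just under the green line, and the amber action is a review of recruitment. The article describes changes to the moderator guide, the choice of game order and moderator influence, but none to attendance or the target. In a condensed article that silence does not prove that no review took place. It does leave 4.5% without visible support. Nor does the article say who recruited for the pilot, so it cannot be taken as given that the route was the same. On non-attendance alone (63/80), about 346 would be analysed with about 84% to 85% power, and the upper confidence limit of 383 just passes 380.

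Some stronger readings should be resisted:
- A reader might infer that the Discussion's statement on unusable responses is false. It concerns nonsensical answers, refusal and poor comprehension. In the pilot that was 3.2% of attenders, within the 4.5% margin. The sentence stands for that purpose; it simply does not cover non-attendance.
- A reader might treat 61/80 as the true rate and call 380 practically impossible. With 80 pilot children, about 1.4% is the fairer figure.
- A reader might set the 77% for the second scenario against the higher power it would have at 105 per arm. The plan states 80%, so the shortfall is about 3 points.
- A reader might add a lower pre-post correlation to deepen the shortfall. The article gives no basis for one, and it has nothing to do with attrition.

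Finally, landing between 260 and 380 is provided for: a missing-values analysis and sensitivity analyses follow, and inference proceeds.

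**Conclusion.** The point holds in conditional form. If the main trial loses children at the pilot rate and 440 is counted at enrolment, as the Recruitment and Statistical analyses sections indicate, about 336 children are analysed (288 to 374 over the CI). Power falls from 90% to about 83% (77% to 87%) in the main scenario, and from 80% to about 77% in the second. The missing-values band is then the expected outcome.

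The base calculation is correct; the fault is an allowance that ignores evidence in the same article. A reader might infer that the trial is badly underpowered. The figures do not show that, because power in the main scenario stays above 80% at the pilot rate. This should be fixed, with moderate severity.

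**What to change.** In Statistical power and sample size and in Statistical analyses, do one of the following.

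1. Base the allowance on the pilot non-attendance. With 440 recruited, state about 336 expected in the ITT set (84 per arm) and about 83% power for d = 0.3, r = 0.75, with the 77% to 87% range. Plan the missing-values analysis as the likely case. This needs no more children; its cost is wording and a less favourable power statement. For scale, keeping 105 analysed per arm at the pilot rate would need 105/0.7625 = 137.7, so 138 per arm or 552 in total.

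2. If 440 is meant to count children who attend, say so and state that non-attenders are replaced. About 426 analysed and 91% power can then be stated. The cost is the extra invitations and a clear account of how replacements are allocated.

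The Discussion sentence on unusable responses can stay, provided it is not presented as covering non-attendance.

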### Statistical analyses

At trial completion, the data will be entered into SPSS, cleaned, screened and the T2 acceptability data separated out for concealment purposes. The concealed dataset will be delivered to the statisticians to conduct analyses.

The primary analysis will be on an Intention-to-Treat (ITT) basis inclusive of all randomised participants who provide some outcome data either immediate post-intervention (T2) or at follow-up (T3). Conclusions will be drawn from the ITT analysis set. In addition, a supplementary per-protocol analysis set, excluding any protocol deviations, will be undertaken. Prior to inferential analysis there will be a validity and verification assessment for data veracity. The primary outcome measure is body appreciation with endpoint being body appreciation immediate post intervention (T2). The primary analysis will be an analysis of covariance comprising randomised arm and body appreciation at T1 as a covariate. This model will include a baseline by covariate interaction term if necessary for model validity. Underpinning assumptions will be assessed for model validity and remedial action taken if required (e.g., robust homoscedasticity corrected analyses or bootstrap approaches as deemed necessary to ensure valid statistical conclusions). If the data is highly discrete to the extent of potentially compromising statistical conclusions, then the linear link function will be replaced by a more appropriate link function (e.g., ordinal logistic regression or negative binomial regression). If the baseline by covariate interaction term is deemed important then a follow-up Johnson-Neyman analysis of covariance will be used. These analysis of covariance models will compare (i) music intervention and music control using the data from the two appropriate arms, and (ii) 15-minute episode intervention and 15-minute episode control using the data from the two appropriate arms. Effect sizes, 95% Confidence Intervals and standardised effects will be reported as appropriate.

The above analyses will be extended to assess any moderating effects by gender, and any moderating effects by year group.

Secondary exploratory analysis will compare the 15-minute intervention and music intervention using the data from the two appropriate arms using the same methodological process.

The above analysis plan for body appreciation will be repeated for the secondary outcome measures of functionality appreciation and weight bias. Secondary research questions at T3 will be examined using the same analysis of covariance methods controlling for baseline (T1).

The aim is to have ITT data on *N* = 420 participants. This will be achieved through a target recruitment of *N* = 440 cognisant that some potential participants might be unable to partake in the research due to external mitigating reasons. If the size of the ITT analysis set is N > = 380 then the data will be analysed as given. If the size of the ITT analysis set due to missing data is between 260 and 380 then a full missing values analysis will be undertaken, and appropriate sensitivity analyses performed. If the size of the ITT analysis set due to missing data is less than 260 then results will be given descriptively.

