## Method

### Study design

A 4-armed randomised controlled trial (RCT) will be conducted to evaluate two media micro-interventions: an approximately 15-minute positive body image episode and a 3-minute positive body image music video. Participants will be randomised using block randomisation, stratified by gender and year group into one of four conditions: (i) 15-minute episode intervention, (ii) 15-minute episode control, (iii) 3-minute music video intervention, or (iv) 3-minute music video control. Randomisation blocks will be in groups of four. The primary outcome for intervention effectiveness is body appreciation, assessed among children pre- and immediately post-intervention and at one-week follow up (T1, T2 and T3). The secondary outcomes for intervention effectiveness are functionality appreciation and weight bias, which will also be assessed among children at T1, T2 and T3. Parents and children will report on intervention acceptability at T2, and parents will report on media re-watch at T3. Parents will provide demographic information for them and their child (T0). A diagram of the research process is presented in Fig. 1.

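### Gender and year group stratify the randomisation but are left out of the primary ANCOVA, so the standard error may be slightly too large (minor)

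*Protocol article*

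**What the plan says.** Under Study design, the protocol article states: "Participants will be randomised using block randomisation, stratified by gender and year group into one of four conditions". It adds: "Randomisation blocks will be in groups of four". With four arms and equal target numbers, this implies one child per arm in each block.

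Under Statistical analyses, the primary model is given by its terms: "The primary analysis will be an analysis of covariance comprising randomised arm and body appreciation at T1 as a covariate". One further term is allowed: "This model will include a baseline by covariate interaction term if necessary for model validity". Each comparison uses only its own pair of arms, for example "These analysis of covariance models will compare (i) music intervention and music control using the data from the two appropriate arms".

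Gender and year group appear only in a later step: "The above analyses will be extended to assess any moderating effects by gender, and any moderating effects by year group". The main model then carries over: "The above analysis plan for body appreciation will be repeated for the secondary outcome measures of functionality appreciation and weight bias". The T3 questions use the same ANCOVA approach, controlling for T1. No reason is given for leaving the stratification factors out of the main model.

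**The concern.** Blocking within the four gender-by-year strata balances these factors between the arms being compared. That removes between-stratum variation from the true sampling error of the arm difference. A model without the factors still counts that variation as residual, so the standard error it reports is larger than the true one whenever the factors predict the outcome beyond T1.

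At stake are the width of the primary confidence interval and the calibration of its p-value, and likewise for functionality appreciation, weight bias and the T3 analyses. The article names the terms of the model, so this is a stated choice and not a detail left to an analysis plan.

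**Working it through.** **Inputs from the protocol article** (Statistical power and sample size): two-sided alpha 0.05, d = 0.3, pre-post correlation r = 0.75, 103 per arm for 90% power, target of 105 per arm analysed.

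**Assumption.** q is the share of T2 variance remaining after T1 that gender and year group explain together. The documents give no value, so 0, 2%, 5% and 10% are shown. Exact balance within strata is also assumed.

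**1. The plan's own figure.** The article says "a sample size of *n* = 103 per arm will have 90% power for an assumed standardised effect of Cohen’s delta = 0.3, with pre-post-correlation of 0.75". The formula is n = 2(1.960 + 1.282)² × (1 − r²)/d². With 1 − 0.75² = 0.4375, this is 2 × 10.507 × 0.4375/0.09 = 102.2, rounded up to 103. It reproduces. The second scenario (d = 0.25, r = 0.8, 80% power) gives 91 against the stated 92, a trivial difference.

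**2. Reported standard error of the planned model** at 105 per arm: √(0.4375 × 2/105) = 0.0913 for every q, because the stratum variation stays in the residual.

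**3. True sampling error** under balanced strata: 0.0913 × √(1 − q). The overstatement is therefore 1/√(1 − q) − 1.

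**4. Actual type I error of the planned model:** the probability that |Z| exceeds 1.960/√(1 − q).

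**5. Power.** The noncentrality is 0.3/(0.0913 × √(1 − q)) with or without the factors, because balance has already reduced the sampling error. Only the critical value differs. For the planned model it is 1.971/√(1 − q) (207 degrees of freedom). For the adjusted model it is the ordinary t value on 205 degrees of freedom. Results are from the noncentral t.

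| q | True SE | SE overstated by | Type I error, planned model | Power, planned | Power, with factors | Gain (points) |
|---|---|---|---|---|---|---|
| 0 | 0.0913 | 0 | 0.050 | 90.5% | 90.5% | 0 |
| 2% | 0.0904 | 1.0% | 0.048 | 90.7% | 91.1% | 0.3 |
| 5% | 0.0890 | 2.6% | 0.044 | 91.1% | 91.9% | 0.8 |
| 10% | 0.0866 | 5.4% | 0.039 | 91.6% | 93.2% | 1.5 |

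Gains are taken before rounding.

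**6. Simulation check** (20,000 trials per setting, 105 per arm, arms balanced within four strata). At q = 10% the planned model reported a mean SE of 0.0915 against a sampling SD of 0.0867; the adjusted model reported 0.0867. Type I error without the factors was about 0.050, 0.044 and 0.040 at q = 2%, 5% and 10%. With them it stayed between 0.049 and 0.052. Power at q = 10% was 91.7% without and 93.2% with the factors. This agrees with the table within simulation error.

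**The case against.** The strongest reply is that the effect is small, harmless in direction and of unknown size. A T1 score taken shortly before T2, with an assumed correlation of 0.75, may absorb most stable differences by gender or age, so q could be near zero. A positive result under the planned model remains valid. Design and analysis also agree with each other: the sample size was calculated for ANCOVA on baseline alone, which is the model specified. All of this stands, and it sets the severity.

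On the other side, the protocol's own hypotheses H3 and H4 expect larger effects in girls and in Year 1. Such moderation would by itself make the factors predictive of T2. As an assumed illustration, take effects of 0.45 and 0.15 SD across the two levels of each factor. The mean difference between levels, averaged over arms, is 0.15 SD. The variance explained is 0.25 × 0.15²/0.4375, about 1.3% per factor or 2.6% together.

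Four stronger readings are tempting, and the documents do not support them:

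- *The analysis disregards the design.* It does not do so wholly: both factors are used in the moderator models, though not in the primary estimate.
- *The omission wastes children.* Dividing 105 by (1 − q), or holding the planned model's power at 90.5% for every q, compares with an unstratified trial. Here stratification has already secured the smaller sampling error, so the power gain is little more than half of what that comparison suggests.
- *The loss must be large for functionality appreciation*, because older children give more answers. That is plausible, but the documents give no figure, and the T1 count is adjusted for as well.
- *Adjustment has no consequences at all.* If the plan switches to ordinal logistic regression, covariates change what the odds ratio means.

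**Conclusion.** The point holds, at minor severity. The stated ANCOVA omits the two factors that stratify the randomisation, for the primary outcome and, by reuse, for the secondary outcomes and T3. The consequence is a standard error that may be slightly too large and a slightly conservative test. There is no bias, no inflated type I error and no shortfall in power on the plan's own assumptions.

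For q between 2% and 5%, the power gain from including the factors is below 1 point at 105 per arm; at 10% it is 1.5 points. These sizes rest on an assumed q, on near-exact balance within strata among the children analysed, and on the protocol's d = 0.3 and r = 0.75. They were worked out for the primary outcome only.

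**What to change.** Specify every ANCOVA, at T2 and T3 and for all three outcomes, as arm + T1 score + gender + year group. Keep the interactions of arm with gender and with year group as the separate exploratory step already planned.

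Carry the two factors into any replacement model as well. If that model is ordinal logistic, state that the odds ratio is conditional on gender and year group.

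The cost is one line of wording and 2 of about 207 degrees of freedom per comparison. Both factors are known before randomisation, so no new data are needed. The change should be fixed before outcome data are examined by arm, so that no choice between adjusted and unadjusted results remains open.
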